**Table 2. Function of the three proteins**

However, the primary candidate formula established in the verification phase is not a formula derived from a quantitative method. While it is useful for comparison between groups such as patient group and normal subject (group), if the test is performed individually without comparison between groups, the decision cutoff value may change every time. Therefore, it was necessary to establish an early breast cancer screening model formula (algorithm) by establishing a test method as a quantitative method capable of individual evaluation rather than comparing between groups, and calculating the appropriate decision cutoff value. After improving the analysis method as a quantitative method, the researchers at this institution established a second formula (algorithm) for the early breast cancer screening model suitable for the quantitative method.

The samples used to develop the early breast cancer screening model formula (algorithm) were plasma samples stored in the biorepository of Lab of Breast Cancer Biology (LBCB), the Cancer Research Institute, Seoul National University College of Medicine.

In addition, to prevent bias in the analysis, the order of the samples used for the early breast cancer screening model formula was randomly mixed and then the samples were anonymized by being assigned non-descriptive numbers from 1 to 200. Sample donor information for early breast cancer and normal subjects was blinded to the researchers until analysis was completed. Utilizing the analyzed data, an early breast cancer screening model formula (algorithm) suitable for the quantitative method was established as a second algorithm through logistic regression analysis.

## 1.2. Benefit/Risk Assessment

There will be no direct benefit to each patient for participation in this study. However, in the absence of a hematological marker for diagnosing breast cancer at present, if the 3 biomarkers show a significant difference before/after treatment (depending on the change in the state of cancer), it could be positioned as a new tool that enables early diagnosis of breast cancer in the future.

Since the test is performed through blood collection, it is judged that the specific side effects and risks predicted for the patient will be minimal.

## 2. Study Objectives, Endpoints

### 2.1. Study Objectives

This study aims to quantify the estimated breast cancer biomarker protein discovered in previous studies using the proteomics technique with LC/MS/MS, and evaluate the clinical efficacy (diagnostic ability) of the multi-marker algorithm and decision cutoff value derived from previous studies using a new sample group (patient group without histological diagnosis).

And advancement of previously discovered biomarkers and development of additional biomarkers.

### 2.2. Study Endpoints

It was set based on the same value as the previous study results.

| AUC   | Sensitivity (%) | Specificity (%) | Positive predicted value (%) | Negative predicted value (%) | Accuracy (%) |
|-------|-----------------|-----------------|------------------------------|------------------------------|--------------|
| 0.771 | 67.0            | 82.0            | 78.82                        | 71.30                        | 74.5         |

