|------------------------------------------|-----------------------------------------------------------------------------------------------------------------------------------------------------------------------------------------------------------------------------------------------------------------------------------------------------------------------------------------------------------------------------------------------------------------------------------------------------------------------------------------------------|
|                                          | 
3) Patients with no history of other cancer diagnoses, including previous breast cancer
 
4) Patients voluntarily participating in this clinical study with an informed consent
 
Healthy control group:
 
1) Patients in BI-RADS category C1-2
 
2) Women over 18 years old
 
3) Patients with no history of other cancer diagnoses, including previous breast cancer
 
4) Patients voluntarily participating in this clinical study with an informed consent
 |
| Exclusion Criteria                | 
Common criteria
 
1) Patients with recurrent breast cancer
 
2) Patients diagnosed with cancer in other organs within 5 years
 
3) Patients with other cancers confirmed by metastasis test
 
4) Systemic condition that makes it difficult to understand and submit informed consent
                                                                                                                                                                                    |
| Number of Subjects                | 
A total of 677 subjects
 
 
- 477 patients with suspected cancer; BI-RADS category <math>\geq</math>C4b
 
- 200 healthy control subjects; C1/2
 
 
*No vulnerable subject included
                                                                                                                                                                                                                                                   |

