**Table 3. Validation baseline used on MASTOCHECK confirmatory study for MFDS approval**

- Area Under the ROC Curve (Concordance index)
- Sensitivity
- Specificity
- Predictive values
- Positive predictive values
- Negative predictive values
- Accuracy

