### 7.2. Data Analysis Procedure

Biomarkers are quantitatively analyzed by the proteomics analysis method for the blood collected through blood collection. The primary breast cancer screening model formula [Result = (0.604 X CAH1 concentration) + (7.7575 X NCHL1 concentration) - (0.523 X APOC1 concentration)] was established by using logistic regression analysis for the 3 proteins (Carbonic anhydrase 1; CAH 1, Neural cell adhesion molecule L1-like protein; NCHL1, Apo lipoprotein C-1; APOC1) finally selected through verification in the previous study. The quantitative analysis results of the obtained samples will be processed by the algorithm and the results will be compared to the results of the previous studies. An independent data management committee will be established to ensure efficiency and objectivity of data analysis and data analysis may include co-investigators and others who are not related to this study.

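### Table 3's PPV and NPV hold only at a 1:1 mix of cancers and non-cancers, which MAST's planned recruitment does not give, so a raw comparison with them would mislead

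*Protocol*

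**What the plan says.** Section 2.2 of the Protocol introduces its endpoint values with "It was set based on the same value as the previous study results". Table 3 then lists AUC, sensitivity and specificity ("0.771 | 67.0 | 82.0") beside PPV, NPV and accuracy ("78.82 | 71.30 | 74.5"). Its caption is "Validation baseline used on MASTOCHECK confirmatory study for MFDS approval". The case mix behind the table is not stated.

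Section 7.2 says that the samples will be run through the algorithm and that "the results will be compared to the results of the previous studies". The Synopsis makes PPV, NPV and accuracy the secondary endpoints.

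The Synopsis plans "477 patients with suspected cancer" (BI-RADS C4b or higher) and "200 healthy control subjects; C1/2", 677 in all. Section 8.1 assumes that 60% of the suspected group have cancer.

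The text points to more than one non-cancer group. The Synopsis (Statistical Considerations) and section 6.1.2 speak of cancer against non-cancer as settled by biopsy. Section 4.1.2 adds C1-2 subjects, who need no biopsy, for comparison with the final cancer patients.

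**The concern.** Sensitivity and specificity are calculated within the cancers and within the non-cancers, so the ratio of the two groups does not enter. PPV, NPV and accuracy depend on that ratio as well. In MAST the ratio comes partly from the decision to recruit 477 and 200 subjects. In the previous study it came from whatever ratio was used there.

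If the two ratios differ, a test that performs identically in both studies yields different predictive values. Set beside Table 3, the difference would read as improvement or deterioration of the device. Two secondary endpoints are exposed to this, and the wording that invites the comparison stands in the protocol itself.

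**Working it through.** **Inputs.** Sensitivity (Se) 0.67, specificity (Sp) 0.82, PPV 78.82%, NPV 71.30% and accuracy 74.5% come from Table 3. Group sizes 477 and 200 come from the Synopsis. The 60% prevalence, 257 cancers, 429 evaluable subjects and 10% dropout come from section 8.1.

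**Formulas**, with p the proportion of cancers:

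- PPV = Se·p / [Se·p + (1 − Sp)(1 − p)]
- NPV = Sp(1 − p) / [Sp(1 − p) + (1 − Se)p]
- Accuracy = Se·p + Sp(1 − p)

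**Step 1: reproduce Table 3.** Per 100 cancers and 100 non-cancers there are 67 true positives, 33 false negatives, 82 true negatives and 18 false positives.

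- PPV = 67/(67 + 18) = 78.82%
- NPV = 82/(82 + 33) = 71.30%
- Accuracy = (67 + 82)/200 = 74.5%

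All three match. Solving each published value back for p gives 0.4999 (PPV), 0.5001 (NPV) and 0.5000 (accuracy). A 1:1 mix is therefore the only one consistent with the table. This fixes the ratio, not the sample size: any 1:1 multiple, such as 134/200 and 164/200, gives the same percentages.

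**Step 2: reproduce the planned mix.**

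- 1.96² × 0.6 × 0.4 / 0.06² = 256.1, rounded up to 257 cancers
- 257/0.6 = 428.3, rounded up to 429
- 429/0.9 = 476.7, rounded up to 477

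Section 8.1 is reproduced.

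**Step 3: hold Se and Sp at the Table 3 values and change only the mix.** Differences from Table 3, in points, are in brackets.

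| Subjects compared | Cancers / total | p | PPV | NPV | Accuracy |
|---|---|---|---|---|---|
| Biopsied cohort | 257/429 | 59.9% | 84.76 (+5.94) | 62.45 (−8.85) | 73.01 (−1.49) |
| Cancers vs C1-2 controls | 257/457 | 56.2% | 82.71 (+3.89) | 65.91 (−5.39) | 73.56 (−0.94) |
| All evaluable plus 200 controls | 257/629 | 40.9% | 72.00 (−6.82) | 78.25 (+6.95) | 75.87 (+1.37) |
| All enrolled | 286.2/677 | 42.3% | 73.16 (−5.66) | 77.24 (+5.94) | 75.66 (+1.16) |

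Here 457 = 257 + 200, 629 = 429 + 200 and 286.2 = 0.6 × 477. If the controls also lose 10%, the pooled figure is 257/609 = 42.2%, with PPV 73.10 and NPV 77.29.

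**Step 4: how far this rests on the 60%.** Over all 677 subjects the mix would be 1:1 if 338.5/477 = 71% of the suspected group had cancer. The biopsied cohort would be 1:1 at 50%. Cancers against 200 controls would be 1:1 with 200 cancers. For a suspected-group prevalence of 40% to 80%, pooled over 677, PPV runs from 59.4 to 82.8, NPV from 86.4 to 65.8 and accuracy from 77.8 to 73.6.

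**Step 5: size of the accuracy shift.** The 95% half-width for accuracy is 1.96 × √[0.759 × 0.241/629] = 3.3 points over all subjects and 1.96 × √[0.730 × 0.270/429] = 4.2 points in the biopsied cohort. The accuracy shift of about 1 to 1.5 points lies well inside both.

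**The case against.** Several objections have force.

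- **Status of Table 3.** The opening sentence of section 2.2 is ambiguous, and the caption ties the table to the earlier approval study. Nothing requires MAST to reach these values, and no decision hangs on them. This stands, and it makes the issue one of misleading comparison on secondary endpoints. It does not remove the issue: the values are listed under this trial's endpoints, and section 7.2 announces a comparison.
- **Method left to the SAP.** How the comparison is made may properly be fixed there. The reference values, however, are fixed in the protocol.
- **The 60% is a planning figure.** The BI-RADS table in section 8.1 allows likelihoods from above 10% (4b) to 95% or more (5), so the actual mix could happen to be 1:1. This stands, and the conclusion is conditional on it.
- **Specificity may not carry over.** MAST's non-cancers include biopsy-negative patients at C4b or higher, whereas the earlier work described in section 1.1 used normal subjects. Specificity and AUC could differ for that reason alone. The fix therefore separates the two kinds of non-cancer.

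Two stronger readings are tempting. A reader might infer that treating the Table 3 sensitivity as exact inflates the rate of false differences. The protocol plans no test against Table 3: section 8.1 sizes the trial for precision, with no null value or performance goal. The sample size behind the table is not given either. A reader might also infer that the 78.82% PPV is claimed for screening, because section 4.1.2 names screening as the purpose. The protocol does not claim that, and it gives no screening prevalence from which to calculate the gap.

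**Conclusion.** The point holds for PPV and NPV. Their Table 3 values belong to a 1:1 mix, and the protocol's own planning figures give about 41-42%, 56% or 60% cancers. With an unchanged test, PPV would shift by −6.8 to +5.9 points and NPV by −8.9 to about +7 points. PPV appears to rise and NPV to fall if non-cancers are limited to biopsy-negative patients or to C1-2 controls; the reverse occurs if both are pooled. Accuracy shares the dependence but hardly moves.

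The result assumes the planned 60% prevalence, sensitivity 67% and specificity 82% whichever non-cancers are used, and a 1:1 mix in the previous study, which is inferred from three agreeing figures and not stated. It does not show that the values must change, that any error rate is inflated, or that the sensitivity reference is affected.

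**What to change.** 1. In section 2.2, remove PPV, NPV and accuracy from Table 3 as reference values. Alternatively, standardise MAST's values to 50% prevalence for that comparison only and say so.
2. Report PPV and NPV calculated from the observed sensitivity and specificity, with confidence intervals, at an intended-use prevalence range that the sponsor states and justifies. Say which specificity is used.
3. Label raw PPV, NPV and accuracy as descriptive of the recruited mix, and state which non-cancers are in the denominator.
4. In section 7.2, limit the comparison with the previous study to sensitivity, and to specificity and AUC against the healthy C1-2 controls. Report specificity and AUC against biopsy-negative C4b-or-higher patients separately.

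This costs some wording and slightly more analysis, with no extra subjects. The PPV reported at an intended-use prevalence is likely to look less flattering than the one in Table 3.

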**Table 3. Validation baseline used on MASTOCHECK confirmatory study for MFDS approval**

- Area Under the ROC Curve (Concordance index)
- Sensitivity
- Specificity
- Predictive values
- Positive predictive values
- Negative predictive values
- Accuracy

## **4. Study Population**

Prospective approval of protocol deviations to recruitment and enrollment criteria, also known as protocol waivers or exemptions, is not permitted.

### **4.1. Inclusion Criteria**

#### **4.1.1. Test Group (breast cancer suspected)**

- Patients who have a lesion of BI-RADS category of  $\geq$ C4b through breast cancer imaging (mammography, ultrasound).
- Women over 18 years old
- Patients with no history of other cancer diagnoses, including previous breast cancer
- Patients voluntarily participating in this clinical study with an informed consent

#### **4.1.2. Control Group (healthy expected)**

- Patients in BI-RADS category C1-2
- Women over 18 years old
- Patients with no history of other cancer diagnoses, including previous breast cancer
- Patients voluntarily participating in this clinical study with an informed consent

Considering that the purpose of this test method is to help screening for breast cancer, we check the possibility of cancer in patients with suspected cancer. In addition, it allows recruiting additional patients corresponding to C1 and C2 in the BI-RADS category that do not require biopsy and compare the blood test values with the final cancer patient.

### **4.2. Exclusion Criteria**

- Patients with recurrent breast cancer
- Patients diagnosed with cancer in other organs within 5 years
- Patients with other cancers confirmed by metastasis test
- Systemic condition that makes it difficult to understand and submit informed consent

### **4.3. Participant Discontinuation/Withdrawal from the Study**

1. Study subject who refuses to proceed with further study procedures (withdrawal of consent)
2. If the subject cannot be followed up
3. In case of violation of selection criteria/exclusion criteria
4. When additional study participation is deemed inappropriate by the judgment of the investigator

## **5. Study Intervention(s) and Concomitant Therapy**

Protein markers will be analyzed in the collected blood. Not an interventional study.

- Using the LC-MS/MS instrument, commercially available stock solution reagents (DTT, IAA, Urea, Trypsin) are used for protein quantification.

### **5.1. Dosage and Administration**

Not applicable (this study does not administer drug/investigational medicinal product)

### **5.2. Concomitant Therapy**

Not applicable (this study does not use comparator)

### **5.3. Discontinuation of Study Intervention**

Not applicable (not an interventional study)

## **6. Study Assessments and Procedures**

### **6.1. Study Assessment**

#### **6.1.1. Observation items**

- Patient's age
- Physical examination (height/weight, body mass index)
- Breast cancer stage (surgical patient-stage based on final pathology result, neoadjuvant chemotherapy patient – clinical stage)
- Surgery method

#### **6.1.2. Assessment items**

- Imaging examination (mammography, ultrasound)
- Quantitative analysis of Carbonic anhydrase 1, Neural cell adhesion molecule L1-like protein, and Apolipoprotein C-1 from collected blood
- Biopsy: For lesions of BI-RADS  $\geq$  C4b in imaging examination, a follow-up biopsy is performed. The results of the biopsy and quantitative analysis of blood proteins will be compared (cancer vs. non-cancer).

## **6.2. Sample Handling Procedures**

### **6.2.1. Sample collection**

For sample collection, 10 ml of blood should be prospectively collected from the patients who agreed to participation in the study. Sample collection should only be performed if the study obtained IRB approval at the participating institution. Collected sample should be aliquoted into 2 EDTA tubes and 2 SST tubes to account for the possibility of hemolysis (2.5ml for each tube). EDTA tubes should be either slowly inverted back and forth or processed with a roller mixer for 5 minutes to mix the sample with the anticoagulant. EDTA tubes should be kept upright and stored at 4°C until centrifugation. The blood contained in the SST tube should be stored at 4°C until centrifugation. Mixing is not required for SST tubes. The time and date of blood collection must be written on the tubes. All collected samples should be shipped to the analysis room on the same day.

### **6.2.2. Plasma and serum separation condition**

In the analysis room, plasma and serum are separated through a refrigerated centrifuge. The conditions are 2,100g (3,000rpm) at 4 °C for 20 minutes. Also, write the centrifugation time so that you can know the refrigerated storage time before separation. Blood collected on the same day should be separated on the same day.

### **6.2.3. Sample preparation**

Separated plasma and serum are aliquoted at 4°C, and samples for stock are stored at -80°C. The pre-treatment of the sample for analysis is through protein denaturation and trypsin digestion so that the target protein contained in the plasma/serum sample can be peptidized, and the final analysis is conducted with MRM (Multi-Reaction Monitoring) mode of LC- MS/MS (Tandem mass spectrometry).

**6.2.4. Target marker concentration analysis**

The concentration of target markers contained in human plasma/serum is quantified using an isotope substitution standard form (heavy peptide) having the same sequence.

**6.2.5. Statistical algorithm analysis**

In this analysis, based on the concentrations of multiple markers, an algorithm that calculates the correlation and weight of these markers to derive optimal diagnostic accuracy is applied to determine the diagnostic accuracy.

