| Duration of Subject Participation | 
Prospective Blood Collection:
 
Study participants will attend the following visits:
 
Visit 1: Informed consent, eligibility criteria evaluation, blood collection
 
 
- If the subject had an imaging before study screening, information can be collected from the previous visit.
 
                                                                                                                                                |
| Number of Sites                   | 1                                                                                                                                                                                                                                                                                                                                                                                                                                                                                                   |
| Planned Study Duration            | 19 JUL 19 – 30 JUN 21                                                                                                                                                                                                                                                                                                                                                                                                                                                                               |
| Statistical Considerations        | 
A prospective clinical trial is to be conducted on undiagnosed patients to confirm the diagnostic capabilities of the developed algorithm.
 
After measuring the concentration of three proteins in plasma (carbonic anhydrase 1, neural cell adhesion molecule L1-like protein, apolipoprotein C-1), an evaluation will be conducted by calculating the following:
                                                                                                                     |

|                |             |
|----------------|-------------|
| Sponsor | Bertis Inc. |
| Product | MASTOCHECK  |

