**6.2.6. Proteomic profiling**

Proteomic profiling of collected blood samples for the advancement of the existing developed markers (to be used in this clinical trial) corresponding to Research Objective 2 and development of additional markers.

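### Section 6.2.5 can be read to let marker weights be optimised in the same analysis that reports accuracy, against the aim of validating an existing algorithm and cutoff; section 7.2 does not settle it

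*Protocol*

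**What the plan says.** Four places in the protocol bear on which rule is applied to the trial samples.

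- **Aim.** Section 2.1 sets out to "evaluate the clinical efficacy (diagnostic ability) of the multi-marker algorithm and decision cutoff value derived from previous studies" in a new sample group. The synopsis (Statistical Considerations) says the trial is run "to confirm the diagnostic capabilities of the developed algorithm".
- **Analysis step.** Section 6.2.5 follows the steps for collection, separation, preparation and quantification of the trial samples. It says that "an algorithm that calculates the correlation and weight of these markers to derive optimal diagnostic accuracy is applied to determine the diagnostic accuracy". It does not name the data from which the weights come, and it does not say that weights or cutoff are fixed.
- **Data analysis.** Section 7.2 says "The quantitative analysis results of the obtained samples will be processed by the algorithm" and that the results are compared with earlier studies. The one formula it prints is the primary one, with coefficients 0.604 (CAH1), 7.7575 (NCHL1) and -0.523 (APOC1). It gives no cutoff.
- **Status of that formula.** Section 1.1, in the text after Table 2, says "the primary candidate formula established in the verification phase is not a formula derived from a quantitative method" and that for individual testing its cutoff could change each time. A second algorithm was therefore built on stored samples. Its coefficients and cutoff are not printed.

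Section 6.2.6 adds a separate activity on the same blood: "Proteomic profiling of collected blood samples for the advancement of the existing developed markers", and development of additional markers.

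**The concern.** A validation study takes a rule that is fixed in advance and measures how it performs in new people. A development study chooses weights and a cutoff that perform well in the data at hand. Section 6.2.5 uses the language of development for what sections 2.1 and the synopsis call validation.

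Three of the endpoints at stake are primary: sensitivity, specificity and the ROC curve. They are to be set against earlier results (Table 3: AUC 0.771, sensitivity 67.0%, specificity 82.0%), and that comparison is interpretable only if the rule is the same one. Were the weights and cutoff re-derived on the trial subjects, two things would follow. The estimates would describe a new model and not the approved software. They would also be optimistic, because the same subjects would both tune and test the model.

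**Working it through.** **1. The texts side by side.** Sections 2.1 and the synopsis speak of an algorithm that already exists. Section 6.2.5 speaks of an algorithm that calculates weights to reach optimal accuracy. To decide between them one would look for a printed rule. Section 7.2 offers only the primary formula, and section 1.1 explains why that formula is unsuitable for individual testing. The second algorithm is mentioned without coefficients, cutoff or version. The protocol alone therefore does not tell the analyst which rule to apply, or that the rule must not be changed.

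**2. The plan's own sample size, which supplies the numbers for step 3.** Inputs from section 8.1: sensitivity p = 0.60, half-width w = 0.06, 95% confidence, prevalence 60%, dropout 10%.

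- n = 1.96² × 0.60 × 0.40 / 0.06² = 256.1, so 257 cancers
- 257 / 0.60 = 428.3, so 429 in the suspected-cancer group
- 429 / 0.90 = 476.7, so 477 recruited

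All three figures reproduce. The biopsy-negative subjects number 429 − 257 = 172. With the 200 controls from the synopsis there are 172 + 200 = 372 non-cancers. Fixing the algorithm changes none of this.

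**3. Size of the optimism if weights and cutoff were re-derived.** Assumptions not in the protocol: three independent normal markers of equal strength, a cutoff chosen at the maximum of sensitivity + specificity, all planned subjects evaluable, and a linear discriminant refit standing in for logistic regression. Total separation is d = √2 × Φ⁻¹(0.771). Optimism is the apparent performance of the refitted rule minus its true performance, averaged over 4,000 simulated trials.

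| Cancers v non-cancers | True AUC | Sens + spec | Sensitivity | Specificity | AUC | Sens + spec, cutoff re-chosen only |
|---|---|---|---|---|---|---|
| 257 v 372 | 0.771 | +3.4 points | +2.0 | +1.4 | +0.003 | +2.9 |
| 257 v 172 | 0.771 | +4.4 points | +1.8 | +2.6 | +0.005 | +3.6 |
| 257 v 372 | 0.60 | +5.3 points | +3.2 | +2.2 | +0.011 | +4.0 |

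Repeat runs with other seeds agree to about 0.1 point and 0.001 in AUC.

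**4. Reading the table.** At AUC 0.771, most of the optimism comes from re-choosing the cutoff. Refitting the weights adds 3.4 − 2.9 = 0.5 points (257 v 372) or 4.4 − 3.6 = 0.8 points (257 v 172). Section 6.2.5 mentions weights but no new cutoff. The planned half-width for sensitivity is 6 points, so an inflation of about 2 points is roughly a third of it.

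**5. A limit of the model.** Table 3 gives 67.0 + 82.0 = 149.0 for sensitivity plus specificity. Under the simulation's assumptions the best attainable sum at AUC 0.771 is 140.0. The model does not match that operating point, so the figures show the order of size and are not a forecast.

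**The case against.** The strongest reply is that section 6.2.5 never says the weights are calculated on the trial data. It stands under sample handling, says the algorithm is applied, and may be a loose account of how the existing algorithm works. Much else supports that reading. Sections 2.1 and the synopsis call the algorithm already derived. Section 7.2 passes results through it without mention of a refit. Section 1.1 says the second algorithm was built beforehand. Section 7.1 gives device approval on 03 JAN 19, before the planned start of 19 JUL 19. This part of the objection stands: a reader might infer that the protocol plans to train and test on the same subjects, and the text does not support that inference.

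A reader might also infer that the marker-development work in 6.2.6 will feed into the primary endpoints. Section 10.6, item 1, places that work after the study of the existing marker's efficacy, on the remaining material, and nothing routes new markers into the endpoints. No candidate number is given for the profiling, so the optimism of a discovered panel cannot be sized from the protocol. How to validate such a panel internally can be left to the analysis plan.

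What does not stand is that the matter can wait for the analysis plan altogether. The protocol makes a positive statement that conflicts with its own aim, and section 7.2, which ought to settle it, points to the superseded formula.

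**Conclusion.** The point holds as a conflict of wording about which rule produces the primary endpoints. It is not a shown bias, and any inflation is conditional on a refit that the protocol does not state.

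If weights and cutoff were re-derived, sensitivity plus specificity would be overstated by about 3.4 to 4.4 points at the prior AUC of 0.771, and the AUC by about 0.003 to 0.005. A weaker true signal would raise this, to 5.3 points and 0.011 at AUC 0.60 (257 v 372). These figures rest on the assumptions in step 3 of the working. The larger consequence would be one of meaning: the estimates would belong to a new model and would not validate the approved device.

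One further assumption is that the approved software carries the second algorithm. Section 1.1 and the approval date suggest so, but the protocol does not say it outright.

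**What to change.** Replace the sentence in 6.2.5, and align 7.2, with wording such as: *The previously established quantitative (second) algorithm, as implemented in the approved software [version], and its decision cutoff [value or document reference] are applied to the trial samples without re-estimating weights or cutoff. All primary and secondary endpoints are calculated from this result. Any re-weighted or extended marker panel is exploratory and is reported separately.*

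In 7.2, present the primary formula as background, or remove it, so that it is not taken for the rule in use. The sponsor should confirm that the approved version is the second algorithm. If the coefficients are confidential, a dated version reference is enough.

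The cost is a few sentences. The sample size stays at 257, 429 and 477, and no procedure changes. If a fixed rule was intended all along, the reported results do not change either.
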